# 1. BACKGROUND

Depressive disorder is one of the most prevalent psychiatric disorders, affecting around 340 million people worldwide ([Hosman, Jané Llopis, & Saxena, 2004](#_ENREF_15)), and is associated with a substantial deterioration in quality of life and economic loss in the community and workplace([Kessler et al., 2006](#_ENREF_19); [Saarni et al., 2007](#_ENREF_29)). Thus, the primary prevention of depressive disorder is an important strategy for global mental health.

A growing body of literature has shown that the intervention programs based on cognitive behavioral therapy (CBT) ([Aaron T. Beck, 1967](#_ENREF_3), [1979](#_ENREF_4)) are effective on improving depression and anxiety among workers. A meta-analysis reported that the estimated effect of CBT was Cohen’s d = 0.68 ([van der Klink, Blonk, Schene, & van Dijk, 2001](#_ENREF_36)). Another meta-analysis reported that the estimated effect of CBT was Cohen’s d = 1.16 ([Richardson & Rothstein, 2008](#_ENREF_26)). Moreover, CBT could be an effective approach for preventing depressive disorder. Two previous meta-analyses have shown that CBT is an effective preventive measure for major depressive disorder ([Cuijpers, Munoz, Clarke, & Lewinsohn, 2009](#_ENREF_7); [Cuijpers, van Straten, Smit, Mihalopoulos, & Beekman, 2008](#_ENREF_9)). However, the implementation of these interventions was still limited, because such a program requires professionals well trained in CBT ([World Health Organization. Department of Mental Health and Substance Abuse., 2001](#_ENREF_37), [2005](#_ENREF_38)). In addition, even if a service is provided, the time, cost, and stigma related to mental health treatment could serve as barriers to access to the effective treatment ([Ruwaard, Lange, Bouwman, Broeksteeg, & Schrieken, 2007](#_ENREF_28)).

An innovative way to deliver CBT-based treatment widely is with a computerized CBT (CCBT) and via the Internet CCBT (iCBT). The CCBT and iCBT programs teach basic information and skills based on the same CBT principles as face-to-face CBT programs do, with a highly structured format comprising educational lessons, homework assignments, and supplementary resources ([Titov, Andrews, & Sachdev, 2010](#_ENREF_35)). Previous studies have shown a significant positive treatment effect of CCBT and iCBT programs on depression and anxiety in the clinical setting ([Andrews, Cuijpers, Craske, McEvoy, & Titov, 2010](#_ENREF_2)). An iCBT program is particularly beneficial with its high anonymity ([Gega, Marks, & Mataix-Cols, 2004](#_ENREF_12)) and high accessibility ([Spek et al., 2007](#_ENREF_33)).

However, no iCBT program is available that would target specifically the general working population, the effectiveness of which would be tested with an randomized controlled trial (RCT). In addition, no previous RCT investigated a beneficial effect of an iCBT program on reducing a risk of depressive disorder which was diagnosed according to standardized diagnostic criteria, such as the DSM-IV ([American Psychiatric Association., 2000](#_ENREF_1)).

The purpose of this randomized controlled study is as follows:

1. to develop a new six-week iCBT program for workers who has subthreshold depressive symptoms in Japan.
2. to examine the effects of the iCBT program on improving the symptoms of depression at three- and six-month follow-ups among workers who has subthreshold depressive symptoms in Japan.
3. to decrease the risk of DSM-IV major depressive episode (MDE) through the six-month follow-up among workers in Japan.
4. to examine the effects of the iCBT program on improving work engagement and work performance at three- and six-month follow-ups among workers in Japan.

The study will be a two-arm, parallel-group, TAU-controlled, non-blinded randomized study.

# 2. OBJECTIVES

## 2.1 Primary question

Our primary question is:

“Among workers with subthreshold depression, will an Internet-based CBT program consisting of cognitive restructuring, assertiveness training, and problem-solving techniques in addition to the standard Employee Assistance Program (EAP) outperform EAP alone, in terms of depression severity (measured with BDI-II) and the onset of major depressive episode (measured with the web-version of the Japanese WHO-CIDI 3.0) at the end of the follow-up survey?”

The primary outcome measures in this study will therefore be:

1. depression severity at three- and six -month post-randomization as measured by the BDI-II
2. the onset of MDE during the 6-month follow-up as measured by the web-version of the Japanese WHO-CIDI 3.0

These two primary outcomes will be used to decide whether or not the intervention was effective.

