## 3.2. Sample size assumptions and estimates

A systematic review of psychological treatments, mostly CBT, for subthreshold depression yielded a Cohen’s d of 0.42 (95%CI: 0.23 to 0.60) at post-test ([Cuijpers, Smit, & van Straten, 2007](#_ENREF_8)). (a Cohen's d of .42 indicates a treatment effect (difference between control mean and intervention mean on the outcome measure) equal to 0.42 standard deviations (where standard deviation(SD) of interest if the SD of the outcome measure)

| Alpha | power | Effect size | N in each cell  (The allocation ratio = 1:1) | Total N |
| --- | --- | --- | --- | --- |
| 0.05 | 0.90 | 0.4 | 131 | 262 |
| 0.05 | 0.80 | 0.4 | 98 | 196 |

Thus, if we randomize 131 in the intervention group and control group for a total of 262 randomized, we will have 90% power to detect a treatment effect assuming that this difference is equal to .40 standard deviations. However, these calculations ignore dropout. We expect that 75% will complete our six-month follow-up, resulting in 98 respondents in the intervention group and control group at six-month. In this situation, we will have 90% power to detect an effect size equal to .47 SD, which is exactly equal to our best estimate of what effect we expect to see at month 4 in this trial.

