### 5.3.2. Data collection

Three-month follow-up (Acute-phase outcomes)

In the intervention group, the primary outcome will be measured at three-month post randomization, i.e. approximately two weeks after the end of the term of learning the iCBT program. In the control group, the endpoint assessment will take place at three-month post randomization.

The outcome data will be collected on the web-based surveys. If no response is received within a week, participants will receive a reminded e-mail asking for completing the web survey. If no response is still available, CRC will send the reminded e-mail to all the participants again.

Six-month follow-up

Both the intervention group and the control group will receive the e-mail which contains information about the URL of research website at six-month post randomization. If no response is received within a week, participants will receive a reminded e-mail asking for completing the web survey. If no response is still available, CRC will send the reminded e-mail to all the participants again.

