### 6.1.4. Analyses of Primary Outcomes

Our two primary outcomes are the BDI-II measure of depression severity and the web-version of the Japanese WHO-CIDI 3.0 measure of the onset of MDE. The BDI-II will be assessed at three- and six-month follow-ups. The Japanese WHO-CIDI 3.0 will be assessed at the six-month follow-up.

The BDI-II is continuous/ordinal variables so will compute the mean score at three- and six-month follow-ups in the two groups, control and intervention. The onset of MDE is discrete variable so will compute the number of incidence at three- and six-month follow-ups in the two groups, control and intervention.

We will first do unadjusted analyses to compare the means using a t-test. We will then do several adjusted analyses. First, ANCOVA or multiple logistic regression analyses will be used to compare the three- and six-month means or the number of incidence on the outcome adjusting for baseline differences on the outcome. We will also do adjusted analyses which control for additional baseline variables, including variables which differ significantly between the control and intervention groups and variables which are strong predictors of the outcome under analysis.

These analyses will be restricted to subjects who complete the three- and six-month follow-ups (all of the statistical methods described above drop from the analysis those with a missing value on the outcome). Since a true intent-to-treat analysis estimates treatment effects based on data from all randomized subjects, not just those who complete a given follow-up, we will also do some mixed-model hierarchical linear models (HLM), using a mixed-model random coefficient model to estimate treatment effects based on all subjects. Subjects are "random effects" with varying intercepts (baseline values) and vary slopes (rates of change from baseline to three- and six-month). The dataset is structured so that each person has up to three records: baseline, three- and six-month follow-ups.

Even subjects who complete only the baseline enter into the analysis and are taken into account when estimating the three- and six-month mean in each group. Such a model can be fit in standard statistical packages such as SPSS, SAS, and STATA.

If conclusions based on the respondent-only and the intent-to-treat analyses are different, we will report intent-to-treat results.

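### Two primary outcomes decide effectiveness, but no rule says whether one or all must succeed, alpha is not controlled, and only a single BDI-II comparison is powered

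*Protocol*

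**What the plan says.** Protocol section 2.1 lists two primary outcomes: "depression severity at three- and six -month post-randomization as measured by the BDI-II", and "the onset of MDE during the 6-month follow-up as measured by the web-version of the Japanese WHO-CIDI 3.0". It then says: "These two primary outcomes will be used to decide whether or not the intervention was effective". The primary question in the same section joins the two outcomes with the word *and*, and refers to the point where follow-up ends. The list beneath it adds three months for BDI-II.

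Section 6.1.4 analyses each outcome separately and mentions no adjustment for multiplicity. For the means it plans a sequence of analyses: "We will first do unadjusted analyses to compare the means using a t-test. We will then do several adjusted analyses". Mixed models on all randomized subjects follow, and their results are to be reported if they disagree with the completer analyses. On MDE, the section says "The Japanese WHO-CIDI 3.0 will be assessed at the six-month follow-up", yet also that it "will compute the number of incidence at three- and six-month follow-ups in the two groups".

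Section 3.2 sizes the trial on one standardized mean difference. The 90% row of its table (alpha, power, effect size, N per arm, total N) reads "0.05 | 0.90 | 0.4 | 131 | 262". No MDE incidence, MDE effect or MDE power appears anywhere in the protocol.

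**The concern.** The protocol itself fixes what decides effectiveness, so this is more than detail left to an analysis plan. Up to three comparisons feed the decision: BDI-II at three months, BDI-II at six months and MDE onset. Suppose BDI-II favours the iCBT and MDE onset shows no difference. The same data could then be reported as effective or as not effective, and the protocol could not settle which.

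Each reading has its own cost. If one success is enough, testing each comparison at 0.05 gives more than a 5% chance of a false positive. If all must succeed, the 80–90% power in section 3.2 does not describe the chance of a positive trial, because it covers one BDI-II comparison only. An analysis plan written later could add an alpha split, but it could not supply power for an outcome on which the trial was never sized.

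**Working it through.** **1. Reproduce the plan's figure.** Section 3.2 gives alpha 0.05, effect size 0.4 and 1:1 allocation. It does not state sidedness; a two-sided test reproduces its numbers.

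- n per arm = 2(z₀.₉₇₅ + z_power)² / d²
- 90% power: 2(1.960 + 1.282)² / 0.16 = 131.3 (plan: 131)
- 80% power: 2(1.960 + 0.842)² / 0.16 = 98.1 (plan: 98)
- Power with 98 per arm at d = 0.47: Φ(0.47·√(98/2) − 1.960) = Φ(1.33) = 0.91 (plan: 90%)

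The arithmetic is sound, for one comparison of means.

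**2. Any one success counts, each test two-sided at 0.05.**

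- Independent tests: 1 − 0.95² = 9.75% for two; 1 − 0.95³ = 14.3% for three.
- Correlated tests, by simulation of correlated normal statistics. The protocol gives no correlations. Assumed: 0.5–0.8 between the two BDI-II tests and 0–0.4 between BDI-II and MDE. Three tests give 11.8–13.6%. One BDI-II time point plus MDE gives 9.3–9.8%.
- Counting only results in favour of the iCBT, three tests give 5.9–6.9% under the same assumptions, against a nominal 2.5%.

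**3. All must succeed.** Joint power cannot exceed the power of the weakest test. Two sample sizes follow from the protocol:

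- Section 3.2: 0.75 × 131 ≈ 98 per arm.
- Section 3.3 expects 245 randomized: 0.75 × 245 / 2 ≈ 92 per arm.

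MDE power was found by exact enumeration of two binomials, with an uncorrected chi-square test at 0.05. Control incidence and a halving of onset are assumptions.

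| Control incidence (assumed) | 92 per arm | 98 per arm |
|---|---|---|
| 3% | 9% | 9% |
| 5% | 12% | 13% |
| 10% | 25% | 26% |
| 15% | 37% | 39% |
| 20% | 48% | 51% |

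Adding the two BDI-II tests lowers these further. With 98 per arm, d = 0.40 and assumed correlations of 0.6 (BDI-II with BDI-II) and 0.3 (BDI-II with MDE), the chance that all three succeed is about 13%, 22%, 31% and 40% at incidence of 5%, 10%, 15% and 20%. Even without MDE, requiring BDI-II to succeed at both time points gives 64–70% at d = 0.40 and 82–85% at d = 0.47 (correlation 0 to 0.6).

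**4. MDE timing.** Section 2.1 defines onset over six months, and section 6.1.4 places the CIDI at six months. The same section then counts incidence at three and six months. If both counts were tested, there would be four comparisons: 1 − 0.95⁴ = 18.5% if independent.

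**The case against.** Several stronger statements are tempting, and the protocol does not support them.

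- *Neither reading keeps the stated error rate or power.* This is wrong. If any success counts, power is at least that of the BDI-II test and only alpha suffers. If all must succeed, alpha stays at or below 5% and only power suffers.
- *The false-positive rate is 12–13%.* This needs three tests, two-sided counting and assumed correlations. Because the primary question asks whether the iCBT outperforms the EAP alone, one can fairly count only false claims of benefit, which gives about 6–7% against 2.5%.
- *MDE is rare, so requiring all outcomes must fail.* The protocol gives no incidence, and its main target group has K6 scores of 5 or more. A favourable case exists: with 131 per arm and no dropout, d = 0.47 and incidence cut from 20% to 6%, the chance that all three succeed is about 88% (correlations 0.6 and 0.3 assumed). The protocol expects 75% completion, however, and with 98 per arm the same case gives about 73%.
- *Section 5.3.2 makes three months the primary time point.* Its statement that "the primary outcome will be measured at three-month post randomization" sits under a three-month data-collection heading, and a six-month paragraph follows. It describes when data are gathered and is weak evidence of a conflict.

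It can also be argued that the *and* in the primary question implies that both outcomes must succeed. It leans that way, but no rule is written, and that reading is the one whose power is never stated.

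**Conclusion.** The concern holds in this form: the protocol makes two outcomes, one of them at two time points, decide effectiveness without a decision rule or alpha control, and it powers only one BDI-II comparison.

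That conclusion needs no assumption. The sizes do. The any-success error rests on assumed correlations, although it exceeds 5% two-sided throughout the range examined and is 14.3% for three independent tests. The power ceiling under an all-must-succeed rule rests on an assumed incidence and an assumed halving of onset. Across 3–20% incidence it stays at or below about 51% after the planned dropout, and only a much larger MDE effect would bring it near the stated power. Because the trial's conclusion depends on the unstated rule, it should be settled before the data are analysed.

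**What to change.** State one decision rule with alpha control in sections 2.1 and 6.1.4. The option that fits the stated sample size is:

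1. BDI-II at six months as the single primary test at two-sided 0.05. This matches the end of follow-up named in the primary question.
2. One named analysis for that test, for example the baseline-adjusted ANCOVA or the all-randomized mixed model already in section 6.1.4. The other analyses become supportive.
3. BDI-II at three months, then MDE onset, each tested at 0.05 only if the preceding test succeeds. Results after the first failure are descriptive. This order holds the family-wise error at 5%.

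Also say in section 3.2 that the 80–90% power applies to the BDI-II comparison only. In section 6.1.4, reconcile counting MDE at three and six months with assessing the CIDI only at six.

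The edit is short, but it has a real cost. Reducing MDE risk is a stated purpose of the trial, and under this order MDE onset could not support a claim of effectiveness by itself. If the sponsor wants it to, there are two alternatives:

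- *An alpha split, for example Holm.* With two tests, the first step at 0.025 needs 156 per arm for 90% power at d = 0.40, or 119 for 80%. With 98 per arm, BDI-II power at that step is 71% at d = 0.40 and 85% at d = 0.47.
- *An explicit rule that both must succeed, with its power stated.* If onset is halved (assumed), 80% power for MDE alone needs about 906, 435 or 199 per arm at control incidence of 5%, 10% or 20%.

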## 2.2. Secondary questions

Secondary outcomes will include:

At three- and six-month post-randomization:

1. depression severity as measured by the Kessler’s psychological distress scale (K6).
2. work performance.
   1. “Effective hours worked” for the past month as measured by the one item from the WHO Health and Work Performance Questionnaire (HPQ).
   2. the number of Sick leave days during past 3 month.
3. work engagement as measured by the 9 Utrecht Work Engagement Scale (UWES).
4. depressogenic schemata as measured by the 24-item Dysfunctional Attitude Scale (DAS-24).
5. improvement of knowledge and self-efficacy regarding five components of the iCBT program (Stress management, Cognitive restructuring, Assertive communication, Problem-solving and Relaxation training) are scored on 5-point scale ranging from 0 (none) to 4 (enough).
   1. knowledge improvement as assessed by asking participants, “How much knowledge do you have about…”
   2. self-efficacy improvement as assessed by asking respondents “How confident are you that you can do….”
6. participant satisfaction as measured by the visual analog scale for satisfaction and a detailed ad-hoc questionnaire for those who received iCBT at the end of the intervention program.

## 2.3. Subgroup hypotheses

The effectiveness of the program may differ according to the initial severity of depression. We will therefore use as one stratification factor high/low subthreshold depression (i.e., participants who scored 5 or more for the K6) at baseline survey, and analyze the results according to these a priori defined subgroups (selective intervention effect), while a sub-analysis will be done for all subjects including those with K6 scores of 0-4, as well. We will also analyze the results according to whole sample (universal intervention effect).

## 2.4. Adverse effects

We expect no adverse health effect from this intervention, except possibly for deterioration in depression (and, ultimately, suicide). We will provide the emergency phone call number and e-mail address at the central office, should any serious suicidal wish occurs. The clinical research coordinator (CRC; [name]), who is a clinical psychologist (MS, MPH), will then deal with the emergency call or e-mail first by himself, and then consult with the clinical supervisors ([name], PhD) to provide appropriate care.

We will measure deterioration in depression in our primary and secondary outcomes. We will measure suicidal attempt, completed suicide and hospitalization at six-month follow-up. We will not implement “stopping decision rules” for this study, because we will not have a sample large enough to determine whether adverse events are clearly related to study participation or if outcome data are sufficient to answer our primary study questions prior to enrollment of the full sample.

[name], the Principal Investigator, will be responsible for all the decisions. [name] will be available for review of all instances of reported adverse effects and suicide risk within 24 hours. When he is not available to fulfill this role because of travel or other obligations, another designated clinical investigator will be appointed to monitor participant safety.

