### 3.3.3. Informed consent

We prepared a website which contained full explanation of the study. Before the baseline survey, participants were invited to read the explanation on the website, and asked to click an “agree” button to show their consent to participate in the study; then they proceeded to the baseline questionnaire page.

Candidates will be informed that their participation is totally voluntary, that even after voluntarily participating they can withdraw from the intervention or from both the intervention and the assessment at any time without stating the reason, and that neither participation nor withdrawal will lead to any advantage or disadvantage at the company. Data of each participant will be handled with sequentially allocated numbers to keep the participant’s confidentiality and kept in a computer not connected to the Internet. It will be accessible to the CRC only.

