### 3.3.4. Intervention allocation

We will randomize eligible subjects to intervention and control groups at a ratio of 1:1. Randomization will be stratified on two variables, namely depression severity at baseline (K6=<4 vs. >=5) and center (company A or company B). Assuming that subjects are recruited from 2 sites, there will be a total of 4 strata. The study statistician will prepare 4 lists of random assignments ahead of time, one for each of the 4 strata. Each list will be blocked to ensure that the ratio of intervention to control is exactly 1:1 at set intervals within each stratum. The statistician will send these lists to the research assistant who is not involved in any other aspects of the study and who will build a spreadsheet that enables concealed sequential allocation and will be responsible for keeping these lists in the safe place.

Before randomizing an individual, the CRC will make a final determination of whether or not the person is eligible to be in the randomized trial. For example, prior to randomization, we will exclude those who having major depressive episode in the past a month. Once the CRC determines the eligibility of the participant, she will enter his/her registration number and the stratification variables to the spreadsheet which will automatically generate the allocation according to the pre-determined random sequence. The entered variables cannot be undone in order to guarantee allocation concealment.

Those randomized to control group will be put on a waiting list and after six-month can receive the iCBT if they wish to do so.

One stratification factor is K6>=5 and K6<=4. The cutoff score for K6 selected based on a previous report, which suggested that 4/5 is the optimal cutoff point for K6 in terms of discriminating community residents and patients with mood and anxiety disorders ([Sakurai, Nishi, Kondo, Yanagida, & Kawakami, 2011](#_ENREF_30)).

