## 4.2. Quality control of treatments

The iCBT program to be used in this study was developed by the investigators based on cognitive-behavioral theory. The exactly same content will be provided to all participants in the intervention group at each session through a web-based learning management system set up at a server of the Department of Mental Health, University of Tokyo.

Concerning tailored feedback comments for a homework which a respondent submits, the homework will be reviewed and commented on by five psychologists at MSc, PhD or post-PhD level. To ensure a similar quality of the feedback comments, a brief guidance and half-day training will be given to these psychologists face to fade by the CRC ([name]), who is also nan experienced clinical psychologist, with a written manual with several examples. All feedback comments to homeworks will be recorded and reviewed by the CRC to monitor the psychologists’ performance and provide additional training to them if necessary.

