## 5.3. Assessment of response variables

### 5.3.1. Independence of the self-reports

In this study, all outcomes will be collected on the web-based surveys. CRC can only access the collected data, in order to assure anonymity and independence of the ratings.

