### 8.2.2. Data and Safety Monitoring Board (DSMB)

The DSMB will consist of the CRC, [name] (biostatistician), and [name] (who is not involved in this study).

The DSMB will meet every three-month after the first client is randomized. The purpose of the meeting will be to review the report prepared by the CRC.

CRC will prepare for the DSMB reports which monitor recruitment progress and data collection (e.g. % completing different follow-ups) and adverse events and their resolution.

We will prepare a free e-mail address and phone number for participants to call up, should they have any suicidal ideation and other significant worsening of their depression. (Cf. 2.4. Adverse events)

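### Suicide attempts and hospitalisation are scheduled for measurement only at month six, although the DSMB reviews adverse events every three months and seats the coordinator who writes its report

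*Protocol*

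**What the plan says.** On timing, Protocol 2.4 states: "We will measure suicidal attempt, completed suicide and hospitalization at six-month follow-up". The same section says that worsening of depression is covered by the primary and secondary outcomes, sets up an emergency phone and e-mail contact, promises review of reported events within 24 hours, and declines stopping rules.

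On oversight, 8.2.2 states: "The DSMB will meet every three-month after the first client is randomized". The board's task is to review a report written by the CRC: "CRC will prepare for the DSMB reports which monitor recruitment progress and data collection", together with adverse events and how they were resolved. On membership: "The DSMB will consist of the CRC", a biostatistician and one person described as not involved in the study.

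On data source, 5.3.1 states: "In this study, all outcomes will be collected on the web-based surveys".

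On the CRC's other duties:
- 3.3.4: "Before randomizing an individual, the CRC will make a final determination of whether or not the person is eligible to be in the randomized trial"; the CRC also enters the participant into the allocation spreadsheet.
- 4.2: "All feedback comments to homeworks will be recorded and reviewed by the CRC to monitor the psychologists’ performance"; the CRC also trains these psychologists.
- 3.3.3, on participant data: "It will be accessible to the CRC only".
- 2.4: the CRC is the first to respond to an emergency call or e-mail.

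**The concern.** The collection schedule for the most serious harms does not fit the review schedule. The board is asked to look at adverse events during follow-up, but the plan produces systematic information on attempts and hospitalisation only as follow-up ends. Before that, an event reaches the board only if someone makes contact.

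A single late measurement also loses information. A participant who answers at month three and not at month six is never asked about attempts or hospitalisation, although a survey was in hand at month three. The protocol's own section on non-response notes that non-completers may be more severely depressed, which is the group in which these events matter most.

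The third strand is independence. The CRC generates, holds and reports the safety information and then sits among those who review it. At stake are the completeness of the harm counts and the independence of the safety review. The primary efficacy comparison is not affected.

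**Working it through.** **Inputs**
- Attempt, suicide and hospitalisation: month six (2.4).
- Measures at month three: BDI-II, K6, HPQ, sick-leave days, UWES, DAS-24, knowledge and self-efficacy (2.2, 5.1). None asks about attempts or hospitalisation.
- Board meetings: every three months from first randomisation (8.2.2).
- Recruitment: two weeks (6.2).
- Survey reminders: one after a week, then another (5.3.2). The second interval is not stated; one week is assumed.
- Six-month completion: 75% (3.2).
- Number randomised: 245 (3.3) or 262 (3.2).

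**Step 1: timeline, in weeks from first randomisation.** Three months is 52/4 = 13 weeks, so meetings fall at about weeks 13, 26 and 39. A participant randomised in week 0 to 2 gets the six-month survey in week 26 to 28. The second reminder follows two weeks later, in week 28 to 30. If everyone were randomised on one day, which 4.1 comes close to, these become weeks 26 and 28.

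| Meeting | Week | Scheduled data on attempts and hospitalisation |
|---|---|---|
| First | 13 | None |
| Second | 26 | Almost none; the survey is only opening |
| Third, if held | 39 | Complete, but follow-up is over |

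**Step 2: participants without scheduled data.** The protocol's own completion figure reproduces: 131 × 0.75 = 98.25, stated as 98 per arm. Non-completion is 1 − 0.75 = 0.25.
- 245 × 0.25 = 61.25, about 61.
- 262 × 0.25 = 65.5, about 65 (with the protocol's rounding, 262 − 2 × 98 = 66).

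These counts assume that the month-six items are asked in the web survey. They cover the planned K6 ≥ 5 sample. If participants in the lower K6 stratum of 3.3.4 are randomised as well, the count rises with the number added.

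**Step 3: who reviews what.** Setting 2.4, 3.3.3, 3.3.4 and 4.2 beside 8.2.2, the CRC's final eligibility decision, allocation entry, monitoring of feedback staff, data access and first emergency response all come before the CRC's report. The CRC is then one of three readers of that report. Only one of the three is stated to be outside the study; the biostatistician's position is not stated.

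**The case against.** The best defence is that 2.4 and 8.2.2 do not formally contradict each other. Section 2.4 creates a continuous reporting stream, with 24-hour review of reported events. Section 5.2.1 adds the company's employee assistance programme and a hotline. Events reported this way can be in the month-three report. There are no stopping rules and no interim analysis, and the Principal Investigator is responsible for all decisions, so late survey data would trip no formal rule.

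Much of this stands, and it rules out several stronger readings that a reader might infer:
- *That there is no systematic harm data before month six.* BDI-II, K6 and sick-leave days are collected at month three in both arms. The gap concerns attempts, suicide and hospitalisation only.
- *That the board cannot do its job.* Early reports need not be empty. They depend on someone making contact.
- *That the CRC votes on its own report.* Voting is not mentioned. The text supports only that the CRC reviews the report as a member.
- *That the plan relies on the web survey to detect completed suicide.* Section 5.3.1 speaks of outcomes, and 2.1 and 2.2 do not list these events among them. The source is unstated.
- *That harms before dropout are all lost, or lost unequally by arm.* A month-six question could look back over the whole period for those who answer it, and both arms receive the same surveys.

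The defence does not meet two points. The absence of stopping rules does not remove the review of adverse events that 8.2.2 assigns. Spontaneous contact also does not replace asking everyone the same question.

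**Conclusion.** The point holds as a matter of harm ascertainment and oversight. Scheduled measurement of attempts, suicide and hospitalisation comes only at month six. The board's month-three meeting therefore has none of it and the month-six meeting almost none. About 61 of 245, or 65 of 262, randomised participants would have no scheduled data on attempts or hospitalisation, including any who answered at month three. Separately, the CRC both writes the safety report and is one of the three members who review it.

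The size rests on 75% completion applying to these items, on web-survey collection, and on meetings held close to the stated three-month interval. The protocol gives no expected event rate, so the number of events missed cannot be estimated. The text between 6.2 and 8.2 is not at hand, so a further safety procedure there cannot be excluded. The point is worth correcting because the remedy is nearly free.

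**What to change.** 1. Reconcile 2.4, 5.3.2 and 8.2.2 by adding the attempt and hospitalisation items to the three-month web survey that both arms already receive. Keep them at month six and state the period each question covers.
2. Say when the board receives them. By the same arithmetic the three-month survey opens in weeks 13 to 15 and its second reminder goes out in weeks 15 to 17. A meeting held exactly at week 13 would see few answers. Holding the first meeting once that survey has closed solves this; otherwise the answers reach the board at about week 26.
3. In 8.2.2, have the CRC prepare and present the report without being a board member.
4. In 2.4, state that deaths are recorded by event report, because a participant's own web response cannot supply them. This is a clarification only.

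The cost is a few survey items at an existing contact and one board seat removed or replaced. No visit or treatment procedure changes. Participants who answer neither survey would still have no scheduled data. How many of the 61 would be recovered to month three is unknown, because the protocol gives no three-month completion rate.
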